### Control arm (SMBG)

Funded glucose monitoring in New Zealand consists of a CareSens glucometer (i-SENS Inc., Seoul, Korea) and test strips. Participants randomised to the control arm will use a Caresens Premier meter, due to the Bluetooth functionality of the device. Participants will have the SmartLog app downloaded onto their compatible smartphone or have SmartLog software set up on their computer. SmartLog is diabetes management software that allows users to view, analyse and share blood glucose data. For participants using SmartLog on their phones, glucose data will be transmitted via Bluetooth when the meter is on and in close proximity to the smartphone. Participants who are unable to use SmartLog on their phones will download data manually to SmartLog on their computer as required. Participants in the control arm will share their glucose data with study staff prior to review points.

Participants in the control arm will receive training on the Caresens Premier Meter and SmartLog software. Training will include: revision of glucose testing technique and glucometer use, pairing the glucometer with SmartLog app on phone, or downloading meter results to SmartLog software, understanding error messages, interpreting glucose trends and graphs on SmartLog and exporting data from SmartLog to the investigative staff. At the end of the RCT phase participants in the control arm will receive the same training on the Dexcom G6 system as the intervention group and use the Dexcom G6 for the continuation phase of the trial (week 12 to 24).

## Glycaemic and cardiovascular risk management

Participants from all localities will be supported by prescribing DNS based at the Waikato study site, with endocrinologist support if required. For all participants, regardless of randomisation, the prescribing DNS will assist participants to manage dietary and lifestyle factors as well as medications, with a focus on participant self-adjustment of insulin during the RCT and continuation phases. Prescribing DNS will follow an insulin titration algorithm (Appendix) to ensure participants receive standardised insulin adjustment advice based on available glucose data. The prescribing DNS will make medication, diet and lifestyle recommendations (as required) at all clinic visits and remote reviews. Medication recommendations will occur as follows:

### Run-in phase

During the run-in phase prescribing DNS will adjust non-insulin glucose lowering medications with the aim to maximise these medications prior to the RCT phase for all study participants. DNS will also assess cardiovascular risk factors and adjust anti-hypertensive and lipid lowering medications in the run-in phase and continuation phase, based on national guidelines [34].

### Randomised controlled trial phase

The RCT phase will be preserved for insulin changes only, unless medication adjustments by DNS are required in this phase for participant safety. For non-urgent cardiovascular risk management during the RCT phase, DNS will request follow up by the participant’s usual care team. Prescribing DNS will provide participants with written insulin titration instructions to follow between scheduled study reviews.

### Continuation and extension phase

During the continuation and extension phases, prescribing DNS will adjust all glucose lowering and cardiovascular medications if required and provide participants with written insulin titration instructions to follow between scheduled study reviews.

## Outcome measures

Study endpoints will follow current international consensus guidelines [35] and include primary and secondary (including binary and composite) endpoints.

### Primary endpoint

The primary objective of this study is to compare the percentage of TIR (3.9–10.0 mmol/L; 70–180 mg/dL) between the intervention and control groups during the last two weeks of the RCT phase. Participants in the control arm will have this collected by blinded CGM during the last two weeks of the RCT phase only.

### Secondary endpoints

#### Secondary efficacy endpoints

The following measures of glycaemic control collected during the last 14 days of the RCT phase (~weeks 10 to 12) will be tested following the primary endpoint in a hierarchical fashion in the order listed below.% CGM time > 10.0 mmol/L (180 mg/dL)% CGM time > 13.9 mmol/L (250 mg/dL)Mean sensor glucose (mmol/L)HbA1c measured at 12 weeks via local laboratory testing% CGM time < 3.9 mmol/L (70 mg/dL)% CGM time < 3.0 mmol/L (54 mg/dL)

#### Secondary exploratory endpoints

All other measures are considered exploratory and will use the false discovery rate to control Type 1 error.% CGM time 3.9–7.8 mmol/L (70–140 mg/dL)Glycaemic outcomes differentiated as 24 hours, day (0600–2359 hours) and night (0000–0559 hours)Glucose variability (expressed as primarily a coefficient of variation and secondly a standard deviation).

#### Binary outcomes

Proportion of participants with:TIR >70% of each dayTIR with ≥5% points improvement from baselineTIR ≥10% points improvement from baselineTime < 3·9 mmol/L (70 mg/dL) for <4% of each dayTime < 3·0 mmol/L (54 mg/dL) for <1% of each dayTime > 10.0 mmol/L (180 mg/dL) for <25% of each dayTime > 13.9 mmol/L (250 mg/dL) for <5% of each day

#### Composite endpoints

Proportion of participants with:Improvement in HbA1c of >0·5% points without an in increase in time < 3.0 mmol/L (< 54 mg/dL)More than 10% points improvement in percentage of TIR without an increase in time < 3.0 mmol/L (54 mg/dL) of >0.5%Mean glucose <8.6 mmol/L (154 mg/dL) and < 1% time < 3.0 mmol/L (<54 mg/dL)More than 70% TIR and < 4% time < 3.9 mmol/L (70 mg/dL)More than 70% TIR and < 1% time < 3.0 mmol/L (54 mg/dL)

#### Cardiovascular profile

The following biochemistry markers and anthropometric measurements will be collected at baseline, week 12 and week 24. Samples for biochemistry data will be collected and processed at local community laboratories.Fasting lipid profileFasting glucoseUrine micro-albuminuriaEstimated glomerular filtration rateFull blood countLiver function testsHigh sensitivity C-reactive ProteinWeightBody Mass IndexBlood pressure

### Psychosocial Factors

#### Sleep quality

The Pittsburgh Sleep Quality Index (PSQI) measures self-reported sleep quality and quantity over the previous month via a 19-item questionnaire. Answers generate seven “component” scores of sleep: subjective sleep quality, sleep latency, sleep duration, habitual sleep efficiency, sleep disturbances, use of sleeping medication and day-time dysfunction [36]. The component scores are aggregated into a global score of 0–21 for adults, with scores higher than five indicating poor sleep. The two items related to sleeping with a bed partner are not included for adolescents.

#### Eating behaviours (4-day diet record)

Participants will be asked to complete a four-day diet record during the run-in phase, and again between week 10 and week 12 of the RCT phase and after 12 months of rtCGM sensor use. The diet record will be completed over three, non-consecutive weekdays and one weekend day on the Research food diary app (Xyris Software (Australia) Pty Ltd) on the participant’s phone. The Research food diary app allows participants to record all food and drinks consumed by searching the food database, scanning barcodes or taking photos. The participants’ diet records will be shared with the investigative staff who will view them in Easy Diet Diary Connect (Xyris Software (Australia) Pty Ltd) and transfer the data to FoodWorks (Xyris Software (Australia) Pty Ltd). Data will be analysed for changes in total energy, macronutrients, and food groups.

### Platform Performance

Platform performance will be gauged by reporting on technical issues with both Dexcom G6 and CareSens/SmartLog systems. Investigative staff will troubleshoot technical issues with participants through the study and record device deficiencies in REDcap. Average Dexcom G6 sensor lifespan information will also be collected throughout the study. Platform performance and usability will also be measured through qualitative interview-based assessment of participant experience using rtCGM (both G6 and G7).

### Health Economic Analysis

If a statistically significant effect on the primary outcome (TIR) is detected, a cost-effectiveness analysis will be undertaken. Cost per percentage point of TIR will be calculated, using incremental cost-effectiveness analysis (ICEA). Costs will be based on the total cost of the trial, excluding costs relating to evaluation of the trial. This conservative approach best approximates the cost of scaling up the treatment across a broader population. In addition, if suitable comparative studies can be found that enable conversion of TIR to Quality-Adjusted Life Years (QALY), a cost-utility analysis will be undertaken. This will calculate the cost-per-QALY-gained, using ICEA.

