## Abstract

**Purpose:**

Improving glycaemic control in type 2 diabetes (T2D) is essential to reducing social and health-economic burden of diabetes-related complications. Continuous glucose monitoring (CGM) has been established as beneficial in improving glycaemic control and reducing hypoglycaemia in people with type 1 diabetes, however data in T2D is limited. This study has been designed to assess the effect of initiating real-time CGM (rtCGM) on glycaemic control in a high-risk population of adults with T2D. Secondary objectives are to assess the cost-effectiveness and safety of rtCGM, and the effects of rtCGM on diet/lifestyle and the burden of diabetic complications, including cardiovascular risk.

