**Methods:**

This multicentre randomised controlled trial (RCT) will be conducted at three sites in New Zealand (Waikato, Christchurch and Dunedin). Eighty adults with T2D on insulin with suboptimal glycaemic control (HbA1c > 8.0% or 64 mmol/mol) will be randomised 1:1 to rtCGM or routine care with self-monitoring of blood glucose levels (SMBG) for three months. This intervention phase will be followed by a three-month continuation phase where SMBG group crossover to use rtCGM. Participants will then be invited to join the extension phase with continued use of rtCGM for a further 12 months. During the extension phase, both groups will independently titrate their insulin under the remote supervision of prescribing diabetes nurse specialists following an insulin titration algorithm. The primary outcome of the study is time in target glucose range (3.9–10 mmol/L or 70–180 mg/dL; TIR). Secondary outcomes include CGM metrics as per consensus statement recommendations, and HbA1c. Additional planned analyses include cardiovascular risk profile, incremental cost-effectiveness analyses, dietary patterns, and qualitative analyses.

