## Methods

### Study design

This multi-centre, randomised controlled trial (RCT) of 80 participants will be conducted in Aotearoa New Zealand over a period of 14 weeks, including a 2-week run-in period for blinded CGM data to be collected from all participants. Following the 2-week run-in period, participants will be randomised 1:1 to either the rtCGM intervention arm (Dexcom G6 rtCGM system (Dexcom Inc., San Diego, CA)) or the control arm (SMBG) with a CareSens premier meter (i-SENS Inc., Seoul, Korea)) for a period of 12 weeks. The primary endpoint will be measured in the final two weeks of the RCT phase (week 10–12), with blinded rtCGM data collected from the control group and compared with unblinded rtCGM data from the intervention group. The 12-week RCT phase will be followed by a continuation phase, where those initially randomised to routine care will cross over into the rtCGM intervention for a further 12 weeks. Following this, participants will be invited to join the extension phase of this study and continue rtCGM use for a further 12 months. As such, the expected duration of subject participation is 78 weeks. At least five visits to the study centre and six ‘remote reviews’ are planned for participants over the study duration (see Table 1). During the 12-month extension phase participants will switch from using the Dexcom G6 system to the Dexcom G7 system, once available.

**Table 1 Tab1:** 2GO-CGM study schedule of assessments

	Baseline	Run-in period 14 days	Treatment period week 1–12				Continuation PERIOD Week 12–24			EXTENSION PERIOD Week 25–77			
	Clinic visit		Clinic visit day 1	Remote review week 2, 8	Week 10–12	Clinic visit end of study week 12	Clinic visit week 12	Remote review week 14, 20	Clinic visit end of study week 24	Week 38 remote review	Clinic visit week 51	Week 64 remote review	Clinic visit end of extension study week 77
Informed consent	X								X				
Demographics	X												
HbA1c Height, weight, BMI	X		X			X	X		X		X		X
Medical review	X					X	X		X		X		X
Blood pressure	X					X	X		X		X		X
Urine pregnancy test	X												
Fasting lipids, FBC, glucose, LFTS, eGFR	X					X	X		X		X		X
Urine ACR	X					X	X		X		X		X
Blinded CGM (14 days)		X			X (control arm)								
Return to clinic after 7 days of blinded CGM for new sensor		X			X (control arm)								
CGM training			X				X						
Electronic review				X				X		X		X	
AE collection		X	X	X		X	X	X	X	X	X	X	X
Sleep quality		X				X							
Food diary		X				X					X		

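### The cost-effectiveness analysis runs only if the TIR result is significant, although it is stated elsewhere as an unconditional objective; its cost base also needs to be defined as a between-arm difference

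*Protocol article*

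**What the plan says.** The Health Economic Analysis section sets a condition: "If a statistically significant effect on the primary outcome (TIR) is detected, a cost-effectiveness analysis will be undertaken". The outcome is cost per percentage point of TIR by incremental cost-effectiveness analysis (ICEA). A cost-per-QALY analysis, also by ICEA, is added if suitable conversion data exist. On costs it states: "Costs will be based on the total cost of the trial, excluding costs relating to evaluation of the trial". The reason given is: "This conservative approach best approximates the cost of scaling up the treatment across a broader population".

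The Abstract attaches no condition. Under Purpose: "Secondary objectives are to assess the cost-effectiveness and safety of rtCGM". Under Methods: "Additional planned analyses include cardiovascular risk profile, incremental cost-effectiveness analyses, dietary patterns, and qualitative analyses".

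Two other statements bear on the cost base. Under Glycaemic and cardiovascular risk management, nurse-specialist care goes to both arms: "For all participants, regardless of randomisation, the prescribing DNS will assist participants to manage dietary and lifestyle factors as well as medications". Under Study design, after the 12-week randomised phase, "those initially randomised to routine care will cross over into the rtCGM intervention for a further 12 weeks".

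**The concern.** There are two separate issues.

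The first is the gate. Cost-effectiveness is an estimation question: what is the extra cost, what is the extra benefit, and how uncertain are both together? A TIR p-value of 0.05 or more does not show that the effect is zero, and it does not answer that question. If the gate stays shut, a stated objective gets no answer. If it opens, the TIR difference in the denominator has been selected for being large, so the cost per point tends to look better than it is unless power is high.

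The second is the cost base. An incremental ratio needs the difference in cost between arms, over a period that matches the effect. The section names the incremental method but describes costs only as those of the trial less evaluation. It does not say that they are split by arm or differenced. A reader cannot tell which ratio will be reported.

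**Working it through.** **Inputs.** From Sample size and power calculation: SD 20; 14 points at 80% power with 33 per arm; 40 per arm enrolled; 78% power for 10 points with 40 per arm and r = 0.58. From Statistical analysis: two-sided alpha 0.05. The document gives no cost figures.

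**Reproducing the plan's figures.**
- n per arm = 2 × (1.960 + 0.842)² × 20² / 14² = 32.04, rounded up to 33. This agrees.
- Residual SD after baseline adjustment = 20 × √(1 − 0.58²) = 16.29. SE = 16.29 × √(2/40) = 3.64. Power at 10 points = Φ(10/3.64 − 1.96) = Φ(0.785) = 78.4%. This agrees with the stated 78%.
- If the stated 18.5 is read as the SD of change, the marginal SD is 18.5/√(2 × 0.42) = 20.2, the residual SD is 16.4 and power is about 77.6%, so the choice of reading does not matter here.

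**Where the gate opens.** The smallest favourable significant estimate is 1.96 × 3.64 = 7.14 TIR points.

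**What the gate selects.** For true difference d, let a = (7.14 − d)/3.64. Then P(significant and favourable) = 1 − Φ(a), and the mean estimate given significance is d + 3.64 × φ(a)/(1 − Φ(a)). A significant harmful result would also open the gate, but its probability is negligible at these effects. For d = 10, a = −0.785, so the mean is 10 + 3.64 × 0.293/0.784 = 11.36. For a fixed cost, the distortion in cost per point is the mean of d/estimate among significant results.

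| True difference | Chance of no analysis | Mean TIR estimate if significant | Mean of d/estimate |
|---|---|---|---|
| 14 (design effect) | 3% | 14.25 (+2%) | 1.04 |
| 10 (plan's second scenario) | 22% | 11.36 (+14%) | 0.93 |
| 7 (assumed; not in the document) | 51% | 9.99 (+43%) | 0.73 |

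The result depends on precision. With 33 evaluable per arm and residual SD 16.29, a true 10 points gives a 30% chance of no analysis, a mean of 11.97 (+20%) and a ratio of 0.88. With 33 per arm and an unadjusted SD of 20, a true 14 points gives 19%, 15.64 (+12%) and 0.95.

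**Cost base.** Let D be the true incremental cost of rtCGM per participant and C the care cost common to both arms, with control device cost near zero. Suppose, purely as an assumption, that C lies between 0.5D and 2D. An undifferenced cost per rtCGM participant is C + D = 1.5D to 3D. The cost of both arms per rtCGM participant is 2C + D = 2D to 5D. Control-arm rtCGM after week 12, if counted, would add more. Each of these raises the ratio, whereas the gate lowers it at modest true effects.

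**The case against.** The strongest reply concerns the numerator. The section names ICEA for both outcomes, and the Abstract also calls the analyses incremental. The cost sentence can be read as naming the source and perspective (delivery costs rather than research costs), with the arms differenced afterwards. A reader might infer that the planned ratio is not incremental, or that post-crossover rtCGM will be charged against a 12-week effect. The text establishes neither: it gives no costing window and does not rule out differencing. Costing detail of that kind is commonly left to a fuller protocol. This objection stands, and it reduces the cost-base issue to a named method and a described cost base that do not visibly fit together.

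On the gate, it can be said that the condition is openly prespecified, that the TIR difference and its confidence interval are reported whatever the result, and that a cost-per-point ratio is unstable when the effect is near zero. It can also be said that at the design effect of 14 points with 40 evaluable per arm the selection is negligible. All of this is true. But instability is a reason to show the uncertainty, not to omit the analysis, and none of it reconciles a conditional analysis with an objective stated without conditions.

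**Conclusion.** The gate is a real inconsistency and should be removed. Its practical size depends on the true effect: negligible at 14 points, moderate at 10 (22% chance of no analysis, cost per point about 7% too low on average), and large only at effects smaller than the plan's own, such as the assumed 7 points (51%, and about 27% too low). These figures rest on a normally distributed estimate, SE 3.64, 40 evaluable per arm and a fixed cost.

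The cost base needs clarifying; it has not been shown to be wrong. Read literally, it includes costs shared by both arms and control-arm rtCGM, and would overstate the ratio.

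A reader might conclude that the plan favours rtCGM overall. The document does not support that: the gate and the literal cost base push in opposite directions, and without cost data the net bias cannot be signed. For the same reason, the section's description of its approach as conservative covers only one of the two. The primary TIR inference is unaffected.

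**What to change.** Delete the significance condition and run the cost-effectiveness analysis whatever the TIR p-value, reporting the joint uncertainty of cost and effect. State that the numerator is the between-arm difference in mean delivery cost per participant over the 12-week randomised phase, so that it matches the TIR contrast. Whole-programme delivery cost can still be reported separately as a scale-up figure, labelled as such.

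The cost is small: a little more analysis, and cost records kept by arm and phase. No extra participants or visits are needed. The downside is a wide interval, or an unstable ratio, if the TIR effect is close to zero.

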### Individual interviews

A purposive sample of participants who have used CGM for at least three months will be invited to participate in individual interviews, either face-to-face or via video conference. Written informed consent will be obtained before beginning interviews. The objective of the qualitative study is to explore the lived experience of participants who have used CGM. Indigenous (Māori) and non-indigenous interviews will be conducted separately to ensure rich data collection from Māori by using a Kaupapa Māori-informed framework [37]. This is a ‘by-Māori, for Māori’ approach to research with Māori that seeks to understand the research question within Māori ways of knowing and being [37]. For Māori, the interview and data analysis will be conducted by Māori research team members and will explore the participant experience of the model of care in 2GO-CGM study. Questions will focus on participant experiences of technology use, nurse prescribing and healthcare education, and the impact of these experiences on Te Ao Māori dimensions of health, including taha wairua (spiritual health), taha whānau (family health), taha hinengaro (emotional health), and taha tinana (physical health) [38]. For non-Māori, the line of questioning will be focused on the experience of wearing the CGM device (acceptability and usability), comparison to self-monitoring of blood glucose levels, and how the device modified participants’ health behaviours. The experience of all participants who have used both the Dexcom G6 and G7 system will also be explored. Data from Māori and non-Māori will be analysed separately via inductive thematic analysis [39].

### Safety/Adverse Events

Adverse events are any untoward medical events that occur during the study. The following adverse events (AEs) will be reported in this study:Adverse device events (ADE): an AE related to the use of the study devices (e.g., CGM, glucometer or phone app).Serious ADE (SADE), or serious AE (SAE): an AE that is fatal, or life-threatening, or causes permanent bodily impairment, or requires hospitalisation, or medical/surgical intervention to prevent serious sequelae.

AEs that do not meet SADE criteria will not be recorded (e.g., respiratory or gastro-intestinal illness). Furthermore, hyperglycaemia and hypoglycaemic events are a frequent anticipated event in insulin users and will not be recorded unless glycaemic excursions are severe and require assistance of a third party, including medical intervention (e.g., hypoglycaemia resulting in altered consciousness and hospitalisation). In these instances, events will be recorded as SAE. SAEs (particularly episodes of HHS, DKA and severe hypoglycaemia) will be notified to the primary investigator/s within 24 hours of the event. Device deficiencies, or technical inadequacies of a device’s quality, durability, reliability, safety or performance, will be assessed as per Good Clinical Practice guidelines (ISO 14155:2020) [40]. Each device deficiency will be assessed for SADE potential and reported to the coordinating principal investigator within one working day if SADE criteria is met. Participant user errors will not be recorded unless they result in a SAE, ADE or SADE. Adverse events will be collected continuously from study onset to study end. Data recorded will include start/stop date of the event, associated symptoms, treatment of event, seriousness, relationship to the investigational device(s), and outcome. All adverse events, regardless of the relationship of the event to the study devices, will be followed up until they have returned to baseline status, stabilised or until ongoing sequelae have been established.

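### The adverse-event recording rule drops non-serious adverse device events that the same section says will be reported

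*Protocol article*

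**What the plan says.** The abstract of the protocol article makes safety a secondary aim: "Secondary objectives are to assess the cost-effectiveness and safety of rtCGM".

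The Safety/Adverse Events section opens its list with "The following adverse events (AEs) will be reported in this study" and names two classes. The first is "Adverse device events (ADE): an AE related to the use of the study devices (e.g., CGM, glucometer or phone app"; it carries no seriousness condition. The second gives one definition for two labels: "Serious ADE (SADE), or serious AE (SAE): an AE that is fatal, or life-threatening, or causes permanent bodily impairment, or requires hospitalisation", continuing to intervention that prevents serious sequelae.

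The next paragraph sets the recording rule: "AEs that do not meet SADE criteria will not be recorded (e.g., respiratory or gastro-intestinal illness". It goes on to exclude glycaemic excursions unless they are severe and need third-party help, and of those it says "In these instances, events will be recorded as SAE". Later sentences require SAEs to be notified within 24 hours, and record participant user errors only when they lead to an SAE, an ADE or a SADE. They also list seriousness and device relationship among the data fields, and state: "All adverse events, regardless of the relationship of the event to the study devices, will be followed up".

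**The concern.** The list and the recording rule cannot both be followed for a non-serious event caused by a study device. The list says to report it. The rule says not to record it unless it meets the criteria for a serious event. Three sites working from this text could resolve the conflict differently.

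What is at stake is the evidence on how well the sensor is tolerated. Non-serious device-related events are the most direct adverse-event evidence on that question, and the Discussion says the authors expect rtCGM to be well tolerated. In the randomised comparison, sensor harms arise mainly in the rtCGM arm, so leaving them out would favour the intervention. An event that was never written down may not be recoverable later.

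**Working it through.** The document gives no figure to reproduce for this point, and no error-rate or power formula applies. The check sets the sentences of the Safety/Adverse Events section side by side, class by class.

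| Event class | Under the list | Under the recording rule, read literally | Result |
|---|---|---|---|
| Non-serious, device-related (ADE) | Reported | Not recorded | Contradiction |
| Serious, device-related (SADE) | Reported | Recorded | Consistent |
| Serious, not device-related (SAE) | Reported | Recorded, since SADE and SAE share one set of seriousness criteria | Consistent, though the label is loose |
| Non-serious, not device-related | Not listed | Not recorded | Consistent |
| Severe glycaemic event needing third-party help | Reported as SAE | Recorded as SAE | Consistent |

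Only the first row fails.

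**Which sentence is out of line?** Three features of the section point to the recording rule.
- ADE is named beside SAE and SADE as a separate trigger for recording a user error. That would be pointless if only serious events were recorded.
- Seriousness is a data field, which has little use if every recorded event is serious.
- The examples of unrecorded events are respiratory and gastro-intestinal illness, which would usually be neither serious nor caused by a device. The intended exclusion looks narrower than its wording.

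**Does anything else capture these events?** Not systematically.
- Device deficiencies (Platform Performance; Safety/Adverse Events) are technical faults, not medical events.
- CGM time below 3.9 and 3.0 mmol/L (Secondary efficacy endpoints) measures hypoglycaemia.
- The interviews (Individual interviews) take a purposive sample of people who have used CGM for at least three months.
- AE collection is scheduled at almost every contact in Table 1, but the recording rule governs what is kept.

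**How uneven is the exposure?** Inputs from Study design: 40 participants per arm (80 randomised 1:1), 12 weeks of rtCGM in the intervention arm, and a blinded sensor in weeks 10–12 (2 weeks) in the control arm. Assuming full wear and no loss to follow-up:
- rtCGM arm: 40 × 12 = 480 participant-weeks of sensor wear;
- control arm: 40 × 2 = 80 participant-weeks;
- ratio: 480 / 80 = 6.

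This covers sensor harms in the RCT phase only. Both arms wear a blinded sensor in the two-week run-in, both use rtCGM in the continuation phase, and the ADE definition also covers the glucometer and the phone app.

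**The case against.** The strongest reply is that the section makes its meaning clear. The list, the user-error sentence, the data fields and the examples all indicate that non-serious ADEs are meant to be kept, so a sensible site would keep them. This is also a condensed article, and the full protocol and case report form may be worded correctly. Part of that stands: it is probably a drafting slip, and nothing here shows that site practice is wrong. But the article states a recording rule, that rule contradicts its own list, and no other section resolves it. This is an error in what is written, not detail left to another document.

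Two stronger readings are tempting, and the document does not support them.

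- *A reader might infer that SAEs unrelated to a device would be discarded.* That requires reading a device condition into the SADE criteria. The shared definition states seriousness criteria only. Severe glycaemic events are recorded as SAEs and SAEs are notified within 24 hours, in neither case with a device condition, and follow-up is explicitly regardless of device relationship. What remains is ambiguity: SADE is spelled out as a serious ADE, an ADE is device-related by definition, and a hospitalised respiratory illness resembles one of the examples of what is not recorded.
- *A reader might infer that the safety objective cannot be answered at all.* SAEs and SADEs (including severe hypoglycaemia, DKA and HHS), CGM time below range and device deficiencies are all still collected. Only the non-serious device-harm component is exposed.

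**Conclusion.** The point holds as an internal contradiction confined to non-serious adverse device events. If the recording rule is followed literally, every such event goes unrecorded and that component of a stated secondary objective is lost. The number of events cannot be given, because the document states no rate and any assumed rate would be illustration only. The direction is clear for sensor harms in the RCT phase, given the sixfold difference in planned wear. The conclusion rests on a literal reading of the rule; sites that follow the list instead would lose nothing. The primary endpoint, the randomisation and the efficacy analysis are not affected.

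**What to change.** Replace the recording sentence with: *AEs that meet none of the ADE, SADE or SAE definitions will not be recorded.* Apply it identically in both arms, and check that the case report form and site instructions follow it. The wording keeps the intended saving on minor intercurrent illness, restores non-serious device events, and removes the ambiguity over unrelated SAEs. The separate sentence on non-severe glycaemic excursions is left as it is. If data collection has begun, send sites a prompt clarification.

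The cost is one sentence, a form and training check, and a few more AE forms.
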